## Abstract

**Background:**

Anorexia nervosa (AN) remains difficult to treat, partly due to co-occurring mental health challenges and gastrointestinal symptoms. Emerging research suggests that individuals with AN exhibit gut microbiota dysbiosis and dysregulation in the gut-brain axis (GBA). However, research examining the role of gut microbiota as a potential driver of AN-related pathologies remains limited. The Norwegian Microbiota Study in Anorexia Nervosa (NORMA) will therefore investigate gut microbiota and its interaction with the GBA in AN.

**Methods:**

NORMA is a collaboration between the Norwegian University of Life Sciences and seven Norwegian specialized eating disorder inpatient treatment units, consisting of three work packages (WP): a clinical observational trial (WP1), in vitro fermentation experiments (WP2), and animal experiments (WP3). In WP1, 90 patients with AN (age 16–50, BMI < 18.5) admitted for treatment and 90 healthy controls (HCs, age 16–50, BMI 18.5–27) will be recruited. Data on mental and physical health, dietary intake, and blood and fecal samples for biomarker and microbiota analyses will be collected at baseline, 6 and 12 weeks after start of treatment for AN patients and once for HCs. Outcomes will be compared between groups, and longitudinal effects of standard treatment examined within the AN group. In WP2, fecal microorganisms from patients and HCs will be grown *in vitro* to assess influence of prebiotics. In WP3, mice will receive fecal microbiota from AN and HC donors to determine if and how AN‑related microbiota affects AN‑relevant phenotypes.

**Conclusion:**

NORMA is pioneering in its integration of clinical, *in vitro,* and animal studies, providing the most comprehensive gut microbiota study of AN so far. By investigating the role of gut microbiota in AN and effects of standardized treatment on gut microbiota composition, this study aims to inform the development of innovative therapeutic strategies and ultimately improve treatment outcomes and life quality for individuals with AN.

**Trial registration:**

NORMA is a registered clinical trial: clinicaltrials.gov as NCT06144905.

## Background

Anorexia nervosa (AN) is a severe eating disorder (ED) associated with high rates of medical complications, psychiatric comorbidities, and mortality [1,2]. The lifetime prevalence of AN in Europe is estimated to be 1–4% [3]. Globally, the AN prevalence is rising, especially among adolescents, and the COVID-19 pandemic may have further increased both the prevalence and severity of the condition [4]. In Norway, approximately 3000 females may require treatment for AN at any given time [5], and the incidence of AN in specialized health care services has increased post pandemic [6]. The etiology of AN remains elusive, yet it is clear that a combination of genetic [7] and environmental factors [8] significantly contributes to its development, with several risk factors identified [9]. Patients with AN often struggle with intense fear of weight gain, low weight, and ambivalence toward recovery, challenges that are compounded by significant gastrointestinal (GI) symptoms [10,11], reported in up to 90% of patients [12]. These factors may complicate treatment, leading to high dropout-rates [13], and present challenges not only to the patients, but also their families, clinicians and society at large, due to the high societal costs involved [14].

Currently, no gold-standard treatment exists for patients with AN. However, specialized care typically combines psychotherapy, nutritional therapy, and management of co-occurring complications and comorbidities. Unfortunately, treatment outcomes are often unsatisfactory [15], with approximately 50% of patients experiencing poor recovery and 20% developing a protracted course [16]. Despite its severity, current dietary interventions are largely based on clinical experience and general guidelines, rather than evidence-based treatments [17], underscoring the need for more effective treatment alternatives. In recent decades, there has been increased focus on the role of gut microbiota in AN, both in its potential involvement in pathogenesis [18] and as a promising therapeutic target [19].

The human microbiota refers to the vast collection of microorganisms that colonize the human body, whose genomes encode more than three million genes that play a significant role in both physical and mental health [20]. The majority of these microbes reside in the GI tract and include bacteria, viruses, fungi, and other microbes [20]. Although the gut microbiota has a heritable component and is affected by age, its composition is mainly influenced by environmental factors, with diet being the most potent modulator [20,21]. Patients with AN often display abnormal dietary patterns, including low energy intake, limited food variety, and fat avoidance [22,23], and patients undergo substantial nutritional changes during treatment. Indeed, substantial evidence reveals that the gut microbiota in individuals with AN is different from healthy controls (HCs), affecting both microbial composition and function [18,24–27]. These differences are often referred to as gut microbiota dysbiosis or imbalance [2,19].

The gut microbiota in individuals with AN has been found to differ from that of HCs in several ways. Multiple studies have reported reduced bacterial richness and evenness in AN, referred to as alpha diversity [19,27–29], with one study showing correlation between reduced bacterial richness and depression as well as core ED psychopathology [28]. However, other studies have found no significant differences in diversity indices between AN and HCs [24–26,30], and findings related to beta diversity are similarly inconclusive [19]. Thus, while there is broad evidence of and compositional alterations (i.e., gut microbiota dysbiosis) in patients with AN compared to HCs [18,24–27], Scala et al. [19] highlight the lack of consensus concerning diversity and psychopathological symptoms in AN.

Due to the contradictory findings on bacterial alpha- and beta diversity measures, recent research on gut microbiota in individuals with AN has shifted the focus toward the investigation of specific microbial taxa [19]. For instance, reduced abundances of the bacterial genera *Roseburia*, *Lactobacillus*, *Faecalibacterium*, *Clostridium*, and *Bifidobacterium* have been associated with anxiety, depression, and AN-related psychopathology [19]. High abundance of the archaeon *Methanobrevibacter smithii* has also been observed in AN [24,30,31], a specie thought to contribute to constipation, a common GI symptom in this population [11]. Additionally, higher abundances of the genus *Sutterella* have been linked to greater weight gain at one year-follow up after treatment, suggesting its potential as a prognostic marker and therapeutic target [26]. Several studies have further associated gut microbiota dysbiosis with AN disease severity [18,28,29], possibly reflecting a metabolically dysfunctional microbial profile [32]. Nevertheless, the specific features of microbial alterations in AN remain unclear due to limited sample sizes, methodological differences, and contradictory findings across studies [19,33].

Particularly, the extent to which gut microbiota dysbiosis in AN normalizes or persists following weight restoration remains understudied, primarily due to the limited number of longitudinal studies that follow the patients throughout their treatment programs [19,33]. Moreover, the existing longitudinal studies often involve short follow-up periods, and many patients remain underweight at the conclusion of these studies, making it difficult to distinguish microbiota changes associated with underweight from those specific to AN. To date, Andreani et al. [26] have conducted the only study with a one-year follow-up, revealing persistent alterations in the gut microbiota composition throughout treatment. Furthermore, even one year after treatment and following weight restoration, the microbiota profile remained partially distinct from that of HCs. These findings align with other longitudinal studies with shorter follow-up durations, which also indicate a partial shift toward normalization during treatment, yet continued divergence from HCs persists [11,24–26,32,34].

The persistent differences in gut microbiota between individuals with AN compared to HCs might imply that the gut microbiota alterations play a causal role in the pathogenesis of AN and/or reinforcing the pathogenic events, rather than being merely a consequence of undernutrition and low body weight. To investigate this hypothesis mechanistically, researchers have turned to animal experiments where gut microbiota is transferred from humans to model organisms [18,35–39], in a procedure known as fecal microbiota transplantation (FMT). Notably, recent studies have demonstrated that FMT from patients with AN and HCs to mice can, to some extent, reproduce AN-relevant behaviors such as anxiety- and obsessive-compulsive-like behaviors [36,38]. Additionally, it has been shown that AN-FMT recipient mice [18], or their offsprings [36], exhibit impaired body weight development compared to HC-FMT recipient mice. In addition to anxiety‑like behavior, a recent study found that germ‑free mice receiving FMT from AN patients also showed reduced food intake, increased physical activity, and elevated inflammatory responses [39]. However, these findings are not universally replicated. For example, Glenny et al. [35] reported no significant differences in body weight changes or body composition in mice receiving FMT from AN donors, attributing the lack of impact to methodological variations and the limited number of human FMT donors [35]. Others have suggested that incomplete microbial transfer from humans to mice also may contribute to these findings [40]. Furthermore, Kooij et al. [37] did not find effects on anxiety-like behavior in AN-FMT experiments with rats. Interestingly, FMT from AN donors has been found to change the expression of endocrine biomarkers, including gene expression of hypothalamic appetite suppressors and hunger hormone [18], and protein expression of the key satiety and appetite regulators peptide YY and leptin [38]. In sum, the evidence for a causal role of gut microbes in AN remains limited, primarily due to the small number of mechanistic animal studies [18,35–38].

The specific mechanisms by which gut microbes could influence metabolic and emotional regulation in AN remain incompletely understood. However, the gut-brain axis (GBA), the bidirectional communication network involving neural, hormonal, metabolic, and immune pathways, is believed to play a central role [41]. Microbial metabolites, particularly short-chain fatty acids (SCFAs) and neurotransmitters, have gained attention as potential key modulators of the GBA. SCFAs, especially butyrate, help maintain gut barrier integrity and modulate immune responses [42]. Individuals with AN show lower fecal SCFA concentrations than HCs, along with reduced abundances of SCFA-producing bacteria like *Roseburia* [11,24,30,43], which have been associated with increased anxiety and depression [30]. The reduced SCFA levels may contribute to a low-grade proinflammatory state in the gut, increasing intestinal permeability [44]. In turn, increased permeability can allow microbial metabolites to enter underlying tissues and the bloodstream, potentially triggering proinflammatory cytokines linked to mood disturbances [19] and possibly contributing to GI symptoms [45]. Although there is limited support from human studies that gut permeability is increased in AN [46], one animal study has suggested a role for gut barrier dysfunction in activity-based AN [47]. Furthermore, low fecal concentrations of the neurotransmitters serotonin, dopamine, and gamma-aminobutyric acid (GABA) have been reported in individuals with AN compared to HCs, supporting a possible link between microbial imbalance and neurotransmitter deficits [24]. Similarly, serum bacterial metabolites in AN may mediate microbiota-related disruptions in appetite, emotion, and behavior regulation [18]. While support from more mechanistic studies is needed, these findings may indicate that gut microbiota dysbiosis seen in AN could contribute to impaired neurotransmitter production, potentially contributing to emotional dysregulation.

Despite growing evidence from both animal and human studies suggesting that the gut microbiota may play a role in AN development and persistence, findings are inconsistent, and the underlying mechanisms remain unclear. This knowledge gap highlights the need for further investigation into the potential causal role of gut microbiota dysbiosis in the onset and persistence of AN, which seems increasingly likely [26]. Furthermore, longitudinal studies in patients with AN during inpatient treatment are scarce and rarely include comprehensive dietary data [19,33], despite diet being central to both AN pathology and gut microbiota composition. Consequently, the impact of AN-specific dietary patterns (e.g., energy restriction, low food diversity, fat avoidance) on the gut microbiota is largely unexplored [22,23,48]. Additionally, gut microbiota changes during and after treatment and weight restoration are poorly understood, partly due to short follow-up periods and patients remaining underweight. Moreover, while some studies have examined the effects of probiotic supplementation on gut microbiota and AN-related pathologies [49,50] prebiotic interventions in AN have yet to be examined [51].

Addressing these gaps is essential for developing personalized, evidence-based nutritional strategies that integrate microbiome modulation into the broader therapeutic framework for AN. To advance the field, larger longitudinal human studies with detailed dietary data and standardized animal models using a larger number of FMT donors are needed. Expanding microbiota research in AN may open new avenues for adjunctive therapies to support psychological recovery, ease GI symptoms, reduce inflammation, and restore nutritional status.

### The Norwegian Microbiota Study in Anorexia Nervosa (NORMA)

The Norwegian Microbiota Study in Anorexia Nervosa (‘the NORMA study’), consisting of three work packages (WP), is the first to combine a longitudinal, clinical observational trial (WP1), in vitro experiments (WP2), and animal experiments in mice (WP3) to investigate the role of gut microbiota in AN. This comprehensive approach is uniquely positioned to address key gaps in literature and advance our understanding of the etiology of AN, as well as the development of microbiota-informed treatments.

The primary aims of the clinical observational trial (WP1) are to identify differences in the gut microbial composition between patients with AN and HCs and to investigate whether standard clinical inpatient treatment with re-nutrition over 12 weeks will have effects on the gut microbiota. Additionally, we will examine the role of gut microbiota for GI problems, gut inflammation and permeability, and mental health outcomes such as anxiety, obsessive symptoms, and depression. Furthermore, we aim to explore how dietary factors interact with gut microbiota to affect these outcomes.

While the clinical trial can provide knowledge on the associations between the gut microbiota and AN features and clinical presentation, the in vitro (WP2) and animal (WP3) experiments will study causation between the AN microbiota and AN-relevant phenotypes and seek to identify prebiotic treatments to normalize gut microbiota dysbiosis in AN. One candidate prebiotic that will be tested is the fiber galactoglucomannan which has been shown to increase the abundance of the SCFA-producing bacteria *Roseburia* in pigs [52], though other candidates will also be evaluated. Because patients with AN often have an extreme fear of calories and rigid dietary patterns, it would be challenging to conduct dietary interventions to test new prebiotic candidates. Thus, the in vitro experimental procedure enables a much easier platform for testing multiple promising prebiotic candidates for targeted treatment of AN to optimize the gut microbiota for tolerable weight-restoration and improved health. The animal experiments will allow for in vivo investigations of human AN-microbiota transplantation in mice on gut-relevant and other AN-relevant features (e.g., appetite, weight development, anxiety- and compulsive-like behaviors) and the impact of candidate prebiotics to treat the AN phenotype.

The long-term goal of the NORMA study is to provide knowledge on the associations between the gut microbiota and AN features and clinical presentation and lay foundations for more specific dietary approaches tailored to AN. Furthermore, we aim to provide the groundwork needed to develop a personalized pharmaceutical solution to treat microbiota dysbiosis in AN. The creation of a non-energy-yielding pharmaceutical supplement to restore the gut microbiota would not only be a feasible clinical approach for AN treatment, but also hold innovative potential in the global pharmaceutical market.

By integrating clinical, experimental, and mechanistic approaches, the NORMA study aims to advance our understanding of the gut microbiota and its interaction with GBA in AN. Ultimately, this research could pave the way for personalized, microbiota-based treatment strategies that improve both physical and psychological recovery in individuals with AN.

## Methods

### The NORMA study

The NORMA study consists of WP1; a clinical observational trial (**Fig 1**), WP2; in vitro experiments (**Fig 2**), and WP3; animal experiments (**Fig 3**). An overview of all WPs is presented in **Fig 4**. The NORMA study is led by the Norwegian University of Life Sciences (NMBU) and conducted in collaboration with seven specialized inpatient EDs treatment units across six hospitals in Norway, located in Oslo, Bergen, Vikersund, Levanger, Bodø, and Gjøvik. Additional collaborators are The University of Oslo, Karolinska Institute and the Norwegian user organizations for eating disorders ROS and SPISFO, which has been involved in the planning of the study. WP1 includes a cross-sectional design that will investigate the microbial composition of the gut in patients with AN in comparison with HCs, and a clinical observational trial that will investigate how the composition is affected by standard care treatment in AN longitudinally (one group time-series design). We will then apply preclinical models in WP2 (in vitro fermentation experiments) and WP3 (animal experiments) based on fecal material from WP1. The first results are expected to be generated during second quarter of 2026.

**Fig 1 pone.0342275.g001:**
[figure not shown]
SPIRIT schedule of enrollment, treatment, and assessments in the clinical observational trial in work package 1 of the NORMA study. AN; anorexia nervosa; HC, healthy controls; NORMA, Norwegian microbiota study in anorexia nervosa; TP, timepoint. Created with BioRender.com.

**Fig 2 pone.0342275.g002:**
[figure not shown]
In vitro fermentation of fecal material from patients with AN and HCs in work packages 2 of the NORMA study. Samples will be anaerobically grown in a rich growth medium, either unsupplemented (control medium) or supplemented with prebiotics such as acetylated galactoglucomannan. The initial setup will include eight pre-fermentation samples (Four HCs and four patients with AN) and 16 post-fermentation samples (Four HCs and four patients with AN per growth medium). AN, anorexia nervosa; HCs, healthy controls; NORMA, Norwegian microbiota study in anorexia nervosa; TP: time point. Created with BioRender.com.

**Fig 3 pone.0342275.g003:**
[figure not shown]
The initial animal experiment in work package 3 of the NORMA study. **(A)** Experimental groups and **(B)** Timeline. AN, anorexia nervosa; FMT, fecal microbiota transplantation; HCs, healthy controls; NORMA, Norwegian microbiota study in anorexia nervosa; PBS, phosphate-buffered saline. Created with BioRender.com.

**Fig 4 pone.0342275.g004:**
[figure not shown]
Overview of the three work packages in the NORMA study. AN, anorexia nervosa; FMT, fecal microbiota transplantation; HCs, healthy controls; NORMA, Norwegian microbiota study in anorexia nervosa; TP, time point; WP, work package. Created with BioRender.com.

### The clinical trial (WP1)

A completed SPIRIT checklist for the clinical trial is provided as Supporting information (**S1 File**)

#### Outcomes.

Primary outcomes for WP1 are: i) differences in fecal microbiota composition between AN and HCs, and ii) changes in fecal microbiota composition-, iii) changes in mental scores-, and iv) changes in GI problems, in AN during standards care treatment at the hospital units for ED.

Secondary outcomes for WP1 are: i) associations between microbiota measures and abundance of specific taxa, serum biomarkers, dietary characteristics, GI issues and mental issues, and ii) associations between baseline microbiota composition and changes in GI complaints during standard care treatment at the clinics for ED, and iii) associations between baseline microbiota composition and changes in mental scores during the standard care treatment at the hospital units for ED.

#### Study participants.

In WP1, a total of 90 patients with AN referred to specialized treatment for ED and 90 HCs will be recruited. Participant recruitment and data collection began on September 1st, 2023, and are expected to be completed by May 31st, 2026.

Patients with a primary diagnosis of AN referred to one of the six collaborating hospitals and who presumably will be under inpatient treatment for at least 12 weeks are eligible for inclusion. The collaborating hospital units include The Regional Department of Eating Disorders (Oslo University Hospital, Oslo), The Regional Department of Eating Disorders (Haukeland University Hospital, Bergen), Regional Center for Eating Disorder (Nordland Hospital Trust, Bodø), The Regional Eating Disorders Unit (Nord-Trøndelag Hospital Trust, Levanger), Modum Bad (Vikersund), District Psychiatric Center (Innlandet Hospital Trust, Gjøvik), and District Psychiatric Center (Oslo University Hospital, Søndre Oslo, Oslo). Both inpatients and patients receiving intensive day treatment are eligible for inclusion. This also includes ‘sequential inpatients’, referring to patients who are hospitalized for 4–6 weeks, then return home for a period, and are subsequently re-hospitalized. The inclusion criteria for the patients are i) female ii) diagnosed with AN (both restrictive and binge-eating/purging type), iii) age 16–50, iv) a body mass index (BMI) below 18.5 kg/m^2^, and v) sufficient proficiency in the Norwegian language to understand and complete questionnaires in Norwegian independently. The exclusion criteria are i) history of inflammatory bowel disease, celiac disease, or GI tract surgery, ii) treatment with oral antibiotics in the past two months, or iv) systematic intake of probiotic supplements in tablet form in the past two months. The inclusion and exclusion criteria are summarized in **Fig 5**.

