The Eating Disorder Examination Questionnaire, version 6 (EDE-Q6.0, for patients with AN only) [53] is a 28-item self-report measure adapted from the interview-based EDE and shows strong correlation with the original version [54]. It assesses the range, frequency, and severity of ED-related attitudes and behaviors across four subscales over the past four weeks: restraint, eating concern, shape concern and weight concern. Higher global scores indicate more severe eating pathology, with a cut-off score above 2,5 suggestive of an ED [55].

The Clinical Impairment Assessment Questionnaire (CIA3.0, for patients with AN only) [56] is a 16-item self-report measure assessing psychosocial impairment related to ED features over the past 28 days. The questionnaire covers mood and self-perception, cognitive functioning, interpersonal functioning, and work performance. The total score ranges between 0 and 48, with higher scores indicating greater psychosocial impairment, and a global score of 16 or above considered to be clinically significant.

The GI Symptom Rating Scale for irritable bowel syndrome (GSRS-IBS, for patients with AN and HCs) [57] is a tool used to measure the severity of irritable bowel syndrome symptoms. The questionnaire consists of 13 self-report items that assess the severity of IBS symptoms across five subscales over the past seven days: abdominal pain, bloating, constipation, diarrhea, and satiety. Scores are rated on a 6-point Likert scale ranging from 1 to 7, with a total score ranging from 0 to 78. Higher scores indicate more severe IBS symptoms, categorized as minimal (0–20), moderate (21–39), and severe (40–78). Permission for use in the NORMA study has been obtained from AstraZeneca on 17th of July 2023.

The 36-Item Short Form Survey (SF-36, for patients with AN and HCs) [58] is a widely used self-report instrument designed to assess quality of life (QoL). The questionnaire includes 36 items that cover eight health domains over the past 4 weeks: physical activity, social activity, health problems, bodily pain, mental health, emotional problems, vitality, and general health perceptions. These are summarized into two components: physical and mental health. Higher scores reflect better QoL, though no universally accepted clinical cut-off values exist. However, scores below 40 are sometimes interpreted as indicating clinically relevant impairment.

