#### Anthropometric measurements and medical records.

For the patients with AN, anthropometric measurements (body height and weight, and body weight history) will be gathered from medical records at each hospital. Results from blood serum analyses and information about medications, including the use of laxatives and dietary supplements, will also be recorded from the patient’s medical records. HCs will report their body weight and height as part of the self-report questionnaires but will be offered the opportunity to have new measurements taken at the hospital if necessary. Anthropometric measurements should be taken within a week of each time point.

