#### Hypotheses and planned statistical data analyses in WP1.

The clinical observational trial in WP1 is designed to test the following hypotheses.

WP1, Hypothesis 1: The gut microbiota in patients with AN is different from that of HCs. We will compare different indices of alpha diversity, investigating both microbial richness and evenness, and different measures of beta diversity. Also, differences in bacterial abundances at various taxonomic levels (e.g., phylum, class, order, family, and genus) will be investigated using conventional statistical approaches as well as more advanced multivariate methods.WP1, Hypothesis 2: Inpatient treatment of patients with AN combining cognitive treatment with re-nutrition strategies will change the gut microbiota in a more normalized direction (more similar to HCs). Mixed models will be applied to statistically analyze the effect of time on different indices of alpha diversity and bacterial abundances at various taxonomic levels (e.g., phylum, class, order, family, and genus) with and without adjusting for baseline characteristics such as age and BMI. Differences in the overall bacterial communities between the patients with AN at the different visits and HCs based on the beta diversity measures will be assessed using methods such as global permutation based multivariate analysis of variance (PERMANOVA).WP1, Hypothesis 3: Gut microbiota composition in patients with AN at TP1 (before treatment) is associated with serum biomarkers such as biomarkers of appetite regulation and inflammation, dietary characteristics, GI issues, and mental issues, and can be used to predict treatment success in terms of improved BMI and EDE-Q-scores. Associations between relevant parameters will be analyzed using multivariate analysis such as principal components analysis (PCA), canonical variate analysis, independent components analysis, and multivariate regression. Regression models will be used to investigate associations between microbial diversity and clinical outcomes, adjusting for age and BMI. Machine learning approaches such as partial least squares regression, gradient boosting, or artificial neural network algorithms will be used to predict the response variables (clinical outcomes and treatment success), from the large set of predictor variables; microbial taxa, gene, or pathway content.WP1, Hypothesis 4: Changes in microbiota composition during inpatient treatment towards that of HCs are associated with improvements in BMI as well as improvements in dysregulated serum biomarkers, GI complaints, and mental health. Associations will be analyzed using similar strategies as described in hypothesis 3.

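### AN subtype is a plausible confounder of the secondary H3/H4 microbiota–outcome associations, and the stated adjustment set (age and BMI) leaves it out

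*Protocol article*

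**What the plan says.** - **Entry criteria** (Study participants): patients are eligible if "diagnosed with AN (both restrictive and binge-eating/purging type", within one patient group. No stratum or quota by subtype is given, and subtype is not mentioned elsewhere in the article.
- **Hypothesis 3** (Hypotheses and planned statistical data analyses in WP1): baseline composition "can be used to predict treatment success in terms of improved BMI and EDE-Q-scores". On the association models the text reads: "Regression models will be used to investigate associations between microbial diversity and clinical outcomes, adjusting for age and BMI".
- **Hypothesis 4** (same section): "Associations will be analyzed using similar strategies as described in hypothesis 3".
- **Hypothesis 2**, by contrast, runs its mixed models "with and without adjusting for baseline characteristics such as age and BMI", which presents the pair as examples. The Hypothesis 3 sentence does not.
- **Background**: of the gut microbiota it says that "its composition is mainly influenced by environmental factors, with diet being the most potent modulator".
- **Anthropometric measurements and medical records**: for patients, "information about medications, including the use of laxatives and dietary supplements, will also be recorded". These variables are collected but not written into the H3 or H4 models.
- **Outcomes**: the associations addressed by H3 and H4 correspond to the secondary outcomes of WP1.

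**The concern.** A confounder of a diversity–outcome association must be related to both sides. On the exposure side, restrictive and binge-eating/purging are labels for different eating and purging behaviour, and the protocol itself ranks diet first among the modulators of the microbiota. On the outcome side, H3 and H4 concern change in BMI, EDE-Q, GI complaints and mental health, any of which could plausibly differ between the subtypes. BMI cannot be assumed to stand in for subtype, since both types enter under the same upper BMI limit.

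If subtype does shift both sides, baseline diversity could appear associated with treatment response when it partly marks a diagnosis already known at admission. The Discussion raises the microbiota as a possible prognostic marker, so the distinction matters for interpretation.

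**Working it through.** **The plan's own figure.** The Sample size calculations section needs 79 per group and allows about 10% drop-out: 79 / (1 − 0.10) = 87.8, so 88, consistent with the planned 90. The 79 cannot be recomputed, because the default settings of the web simulator are not listed. It concerns AN versus HC and is used here only to set n: 79, or 90 × 0.9 = 81.

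**Inputs from the protocol.** n of about 80; α = 0.05 (taken as two-sided, since sidedness is not stated); adjustment for age and BMI.

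**Inputs assumed, because the article gives none.** Binge-eating/purging share p of 30% to 50%; subtype differences d_m in diversity and d_y in outcome change, each in within-subtype SDs and set equal; no true microbiota effect.

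**Spurious slope when subtype is left out.**

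b = p(1 − p)·d_m·d_y / [1 + p(1 − p)·d_m²]

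The numerator is a product, so a subtype difference on one side only produces no bias. With p = 0.4, p(1 − p) = 0.24:

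- d = 0.3: 0.0216 / 1.0216 = 0.02
- d = 0.5: 0.0600 / 1.0600 = 0.06
- d = 0.8: 0.1536 / 1.1536 = 0.13

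**False-positive rate of one test, by simulation.** The first pair of columns uses 20,000 datasets per setting, n = 81, p = 0.4, no other covariates. The second pair uses 8,000 datasets per setting, n = 79, with age and BMI in the model, at p = 0.3 / p = 0.5.

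| d on both sides | n = 81, subtype omitted | n = 81, subtype added | n = 79, age and BMI only | n = 79, age, BMI and subtype |
|---|---|---|---|---|
| 0.3 SD | 0.053 | 0.049 | 0.053 / 0.053 | 0.048 / 0.048 |
| 0.5 SD | 0.078 | 0.051 | 0.067 / 0.073 | 0.053 / 0.051 |
| 0.8 SD | 0.218 | 0.049 | 0.171 / 0.222 | 0.050 / 0.054 |
| 1.0 SD | not run | not run | 0.324 / 0.415 | 0.050 / 0.048 |

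**Does BMI adjustment absorb it?** With the subtypes also 0.5 SD apart in BMI, p = 0.4 and d = 0.8, the rate with age and BMI in the model is still 0.186 and the mean spurious slope 0.125.

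**The case against.** **The adjustment set may not be closed.** The H3 sentence names age and BMI but does not say that nothing else will be used. H4's similar strategies need not mean an identical covariate list, and an analysis plan that is not shown could widen both. This stands as a limit. The point remains because the article does state a set for H3, without the open wording it uses for H2, and the set omits a variable implied by the entry diagnosis.

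**The links are plausible, not documented.** No section says that the subtypes differ in microbiota, diet or treatment response. The EDE-Q description begins "It assesses the range, frequency, and severity of ED-related attitudes and behaviors", and a reader might infer that subtype is built into this success measure. The description goes on to four subscales (restraint, eating concern, shape concern, weight concern) and a global score, with no binge or purge score named. H3 also concerns improvement, and a difference at entry does not imply a difference in change. H4 would further need the subtypes to differ in microbiota change. All of this stands.

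**Tempting stronger readings.** A reader might infer that the prediction models are invalid. They are not: a marker of subtype can still predict, and what stays untested is its added value over subtype. A reader might also infer that the primary analyses are compromised. H1 asks about AN as a whole against HCs, so pooling answers the question posed. H2's effect of time is within patients, so a fixed characteristic does not confound it, leaving drop-out aside.

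**Why subtype and not site or medication?** The same argument can be made for other variables, and diet and laxative use measure the suggested pathway more directly. That is fair, but those variables are not named in the H3 or H4 models either, and subtype costs almost nothing to add.

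**Conclusion.** The concern holds as a possible confounding of the secondary H3 and H4 associations, not as a demonstrated bias. The textual basis is firm: both subtypes are enrolled together, the H3 regressions name age and BMI, H4 follows them, and subtype enters no stated WP1 analysis.

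The size rests wholly on assumed subtype shares and effects. At 0.3 SD on both sides there is no material inflation, and at 0.5 SD the rate is 7–8%. It reaches about 20% only when the subtypes differ by around 0.8 SD in both diversity and outcome change. In every simulated setting, adding subtype brings the rate back to about 5%. This is an inexpensive improvement to a stated model; it does not call the design or the primary comparisons into question.

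**What to change.** 1. Confirm that AN subtype (restrictive or binge-eating/purging), taken from the qualifying diagnosis, is recorded at TP1. The entry criterion implies that it is known, but the article does not list it as an analysis variable.
2. In the H3 association regressions, and in those for H4, name the covariates as age, BMI and TP1 subtype.
3. Include subtype among the clinical predictors against which the microbiota-based prediction models are compared, so that any claim of prognostic value is a claim of added value.

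Cost: a change of analysis wording and one degree of freedom per model. No new data are needed if subtype is already recorded. Settling it before the H3 and H4 analyses avoids a post-hoc choice of covariates. Contrasts of each subtype with HCs under H1 are optional; they would be less precise and should be labelled as supporting if shown.
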